# Data and Specimen Banking

The primary storage platform for study data will be the SRAlab REDCap (Research Electronic Data Capture) system. Any forms/paper documentation will also be maintained within study binders and/or uploaded into REDCap. REDCap is a secure web-based application for building and managing online databases for research studies. REDCap can be used to collect virtually any type of data and is specifically geared to support online or offline data capture for research studies and operations.

Sensor data will be stored and maintained by [name] group (at SRAlab) for analysis. Videos acquired during collection of sensor data will be maintained on a secured HIPAA-compliant AWS.

De-identified data or limited datasets will be shared with other investigators. Investigators from outside the study will be asked to sign an agreement of confidentiality in order to receive the de-identified data or limited datasets requested. Data use agreements will be in place between all actively enrolling, participating sites and SRAlab. The PI will be responsible for receipt and transmission of data. Data will be stored for at least 7 years. We plan to archive de-identified data in a data repository for future use by other researchers, after the study is completed.

No specimens will be collected as part of this study

# Sharing Results with Participants

Results of assessments completed during assessment sessions will be provided to families. during the clinic visit, as available. Some assessments require calculation of results, which will be done after the session and these results will be made available on request. Assessment results will also be provided to the child’s clinical care team if performed in the home, outside of the clinic. Information obtained from sensor data will not be provided to families.

The assessments completed during the course of this study may indicate a generalized diagnosis of motor delay or a specific diagnosis, for example, cerebral palsy. Given that we intend to perform the assessments in the Early Childhood Clinic, most families will be informed of this by the Early Childhood Clinic team. If the assessments are performed in the infant’s home due to a missed clinic visit, this information will be provided to the infant’s medical team, who may discuss these findings with the family and ensure the appropriate referrals are made.

# Study Timelines

Infants may be involved in the study for up to two years corrected age. The intervention group will receive therapy at a target dosage of 2 X per week until 12-months corrected age; both intervention and standard of care groups will participate in assessments until 12-months corrected age. Participants may also be asked to complete optional assessments at 18-month and 24-months corrected ages, if these time points occur while the overall study is still ongoing. These later time points are not required as part of the study, but may provide useful information on the longer-term effects of the intervention.

# Vulnerable Populations

The research involves infants from birth to 24-months corrected age who are at risk of motor or other developmental delay.

# Participant Population(s)

| Accrual Number: | Category/Group:  (Adults/Children Special/Vulnerable Populations) | Consented:  Maximum Number to be Consented | Enrolled:  Number to Complete the Study or Needed to Address the Research Question |
| --- | --- | --- | --- |
| Local: Lurie/Prentice  UIC | Infants | 180 | 123 |
|  | Infants | 60 | 31 |
| Total: |  | 240 | 154 |

# Recruitment Methods

The primary recruitment method is noted above under screening procedures. All participants will be identified during their NICU stay. Participants may be consented up to 48 weeks PMA.

# Compensation for Participation in Research Activities

For intervention visits, the cost of parking may be reimbursed for families who complete visits within a clinic setting. If cost of transportation is an issue for any family, reimbursement may be offered, on an individual basis. All participants (intervention group and standard of care group) will be compensated at a rate of $100 per assessment time-point. Participants may also be provided with a parking voucher. All payments will be provided by SRAlab via a ClinCard upon completion of the set of assessments corresponding to each time point (assessments may be completed over more than one session, if necessary).

In addition, payments will be made on a monthly basis to all participants who remain in the study, according to the following schedule: months 1-3: $25 per month; months 4-6: $50 per month; months 7-9: $75 per month; months 10-12: $100 per month.

If participants miss an assessment time point, they will not be reimbursed for the assessment visit. If they do not comply with other study requirements, such as completing surveys, their monthly payments will be stopped until their next scheduled study activity is completed. Monthly payments and assessment payments will resume after they complete the next scheduled study activity.

Focus group participants will be paid $100 per session completed. Parking may be reimbursed if applicable.

Participants will be informed that payments in excess of $600 in a calendar year are reportable to the IRS as taxable income

# Withdrawal of Participants

Participant families will be informed that their participation is strictly voluntary and that they can withdraw from any experiment at any time for any reason without consequence. Participants may be withdrawn from the research based on PI discretion regarding medical stability or compliance to study requirements. If a child is transferred from the NICU to the Pediatric Intensive Care Unit (PICU), they will be dropped from the study.

If subjects are withdrawn from the study after data has been collected, the data will be retained if it is deemed to be scientifically relevant by the researchers. Data that is not relevant will be discarded.

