# Procedures InvolveD:

*Setting:* This study will have three primary recruitment sites including: Ann & Robert H. Lurie Children’s Hospital of Chicago (Lurie), Northwestern Medicine Prentice Women’s Hospital, (Prentice) and the Children’s Hospital at the University of Illinois (UIC). Shirley Ryan AbilityLab (SRAlab) will serve as the Data Coordinating Center. All sites will work collaboratively to manage logistics, recruitment, intervention development, intervention delivery, assessment, data analysis, and dissemination/publication of results. A data use agreement (DUA) will be in place for all actively enrolling sites to govern the transfer of research data between sites.

*Recruitment:* Study team members at each recruitment site will screen infants admitted to the NICU via an electronic medical record review. Staff will confirm participant eligibility criteria (see inclusion and exclusion criteria above) overall medical stability, and family readiness prior to approaching for study introduction and consent. Caregivers of eligible infants who are cleared to approach but not available during normal working hours may be initially contacted through written materials and/or telephone or email to (i) determine their general interest in study participation and (ii) to ask when they next plan to be in the NICU so that staff can arrange to approach the family in person. Recruitment monitoring will be completed either locally or in REDCap.

*Informed Consent*: Identified staff will provide a study overview, review participation requirements, and complete the informed consent with parents. It is anticipated that infants will be screened at approximately 33-34 weeks post-menstrual age (PMA). Infants may be consented up to approximately 48 weeks PMA. Participants will be considered enrolled in the study upon completion of the informed consent.

*Randomization:* Randomization will be completed after participants are consented. Participants will be randomized at their respective recruitment site. Neonatologists at Lurie, Prentice, and UIC will review infant medical history and stratify the infants based on their risk for neuromotor delay (mild or moderate-severe) using the following criteria, to ensure a balanced matching of impairments across study groups:

*Mild risk:*

- At risk for Hypoxic Ischemic Encephalopathy (HIE) (10-minute Apgar <7 plus pH<7.15 or base deficit >/=12)
- Clinical HIE diagnosis or meningitis with normal MRI and no seizures

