*Assessments*: All enrolled participants will follow the same assessment timeline (Table 1). Assessments will be completed at study enrollment and thereafter at monthly intervals up to 3 months corrected age, then at 3-months corrected age, 6-months corrected age, 9-months corrected age, 12-months corrected age, 18-months corrected age (optional), and 24-months corrected age (optional). The number of assessments prior to 3 months corrected age will vary by preterm status and age of enrollment. If infants are unable to complete a scheduled assessment session, efforts will be made to re-schedule. Flexibility in location (home vs. in-clinic) of assessment will be made available as necessary. Families will be screened for COVID-19 prior to each assessment session. If any member of the family is unwell or there is a known exposure to COVID-19, the session will be rescheduled or conducted via telemedicine where possible, following hospital guidelines. Assessments may be completed over several days depending on caregiver and infant needs. If infants are unable to complete a testing session, their participation in the study will not be impacted, however, the study team will appropriately document this issue. Assessment therapists will self-screen for COVID-19 symptoms or exposures before starting work each day, and will follow all clinic COVID-19 protocols. **Assessments in** **bold** in Table 1 are part of standard clinical care in the Early Childhood Clinic and would be done regardless of study participation (i.e., these are not study-specific procedures).

*Primary Outcome Measure:* Bayley-4 motor score at 12-months corrected age

*Secondary Assessments and/or Outcome Measures:* Sensors, PedsQL, Bayley-4 (cognitive)

*Exploratory Assessments and/or Outcome Measures:* GMA, NSMDA, TIMP, HINE, AIMs, PEDI-CAT, WIDEA-FS

*Assessments*:

| **Enrollment: Pre-term or Term Age** | **Monthly up to 3 months CA** | **3-months CA** | **6-months CA** | **9-months CA** | **12-months CA** | **18-months CA** | **24-months CA** |
| --- | --- | --- | --- | --- | --- | --- | --- |
|  |  |  | **Bayley-4^§^** |  | **Bayley-4^§^*** | **Bayley-4^§^** | Bayley-4**^§^** |
| **GMA**** | **GMA** | **GMA** |  |  |  |  |  |
|  |  |  | AIMS | AIMS | AIMS |  |  |
| Sensors | Sensors | Sensors | Sensors | Sensors | Sensors | Sensors | Sensors |
|  |  | NSMDA |  | NSMDA | NSMDA | NSMDA | NSMDA |
| TIMP | TIMP | TIMP |  |  |  |  |  |
|  |  | **HINE** | **HINE** | HINE | **HINE** |  |  |

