### Randomization:

Participants (including those in the pilot study) will be randomized to the two treatment arms using the method of permuted blocks. Randomization sequences will be generated by a statistician, and will be uploaded into the REDCap randomization module. Randomization will be stratified by study site and by risk of neuromotor delay (mild vs. moderate/severe). Siblings in multiple births will be assigned to the same group, and outcomes assessed only for the infant with the most severe risk. In order to ensure unbiased evaluations, assessments of motor function and other outcomes will be performed by different study team members than those administering treatment, and although this is not a blinded study, therapists conducting study evaluations will be blinded to treatment arm assignment whenever possible.

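### The withdrawal rule does not separate stopping study therapy from leaving the study, so the infants with a 12-month Bayley-4 score may differ from those randomised

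*Protocol*

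**What the plan says.** Protocol, Withdrawal of Participants, gives two routes out besides the family's own choice. One is discretionary: "Participants may be withdrawn from the research based on PI discretion regarding medical stability or compliance to study requirements". The other is mandatory: "If a child is transferred from the NICU to the Pediatric Intensive Care Unit (PICU), they will be dropped from the study". Both remove the infant from the study, not only from the study therapy. For data already in hand when an infant is withdrawn, the section says that "the data will be retained if it is deemed to be scientifically relevant by the researchers. Data that is not relevant will be discarded". It gives no criteria for relevance, and does not say when the judgement is made or whether it is made blind to arm.

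These rules can act after allocation. Under Procedures Involved, "Randomization will be completed after participants are consented", and the first intervention block runs from enrolment to NICU discharge. A PICU transfer can therefore follow randomisation.

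On blinding, the Randomization section says that "although this is not a blinded study, therapists conducting study evaluations will be blinded to treatment arm assignment whenever possible". No blinding is stated for the PI or for the researchers who judge relevance.

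The primary analysis (Data analysis) is a two-sample t-test on the 12-month Bayley-4 motor score. The missing-data remark in that section concerns the mixed models for Aims 2 and 3. In Table 1 the 12-month Bayley-4 is in bold, and bold assessments "are part of standard clinical care in the Early Childhood Clinic and would be done regardless of study participation".

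**The concern.** The grounds for withdrawal are not neutral. Medical instability and PICU transfer are plausibly related to motor outcome. Compliance is plausibly related to family engagement and so to outcome, and there is more to comply with in one arm: study sessions and the Activity Playbook (a target of at least 5 days a week) are asked of the intervention arm only. Control families have assessments and surveys, so their exposure is smaller but not nil.

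If an infant leaves the study before 12 months for such a reason, the primary score is not collected. If this happens more often in one arm, or to infants with a different prognosis in one arm, the t-test compares groups that randomisation did not form. A difference can then appear without a treatment effect, or a real one can be distorted.

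The discard sentence adds a second, smaller problem. It lets people not stated to be blinded decide, case by case, which sensor, PedsQL and other pre-withdrawal data remain. The mixed models for Aims 2 and 3 rely on using all evaluable observations.

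**Working it through.** **Reproducing the plan's figures (Power Analysis).** Inputs: 77 per arm, difference 8 points, SD 15, two-sided alpha 0.05.

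- Power from the noncentral t distribution: 90.8% (stated 90.1%). With SD 17.5: 80.5% (stated 79.4%). Both agree to within about one percentage point.
- Attrition: 154 / 0.70 = 220 (stated 220); 154 / 0.80 = 192.5 (stated 192).

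The attrition allowance secures the number evaluable. It does nothing for comparability.

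**Bias from selective removal.** Suppose a fraction p of an arm is removed and would have scored on average D points below the rest of that arm, whose mean is m. The full-arm mean is (1 − p)m + p(m − D) = m − pD. The mean of those who remain is m, so removal raises the arm mean by pD. The bias in the difference (intervention minus control) is

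b = p_I × D_I − p_C × D_C.

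If p and D are equal in both arms, b = 0.

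**Effect on the test when there is no true difference.** SE = 15 × √(2/77) = 2.417. The rejection rate is P(Z > 1.96 − b/SE) + P(Z < −1.96 − b/SE). This takes 77 evaluable per arm, an unchanged SD of 15, and the fixed-sample critical value 1.96.

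The Protocol gives neither p nor D, so the values below are assumptions. All remove infants from one arm and none from the other.

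| p | D (points) | b = pD | b/SE | Type I error | b as share of 8 |
|---|---|---|---|---|---|
| equal in both arms | equal in both arms | 0 | 0 | 5.0% | 0% |
| 5% | 7.5 | 0.375 | 0.16 | 5.3% | 5% |
| 10% | 8 | 0.8 | 0.33 | 6.3% | 10% |
| 10% | 15 | 1.5 | 0.62 | 9.5% | 19% |
| 15% | 15 | 2.25 | 0.93 | about 15% | 28% |

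The third row in full: 0.8 / 2.417 = 0.331; P(Z > 1.629) + P(Z < −2.291) = 0.052 + 0.011 = 0.063.

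The sign depends on which arm loses the infants. Loss of low scorers from the intervention arm favours the intervention; loss from the control arm works against it.

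**Which data each rule touches.** An infant withdrawn before 12 months has no primary score to discard; what is lost is the follow-up visit. An infant withdrawn after 12 months, during the optional 18- and 24-month follow-up, already has a primary score, which could hardly be called irrelevant. The dropping rule therefore bears on the primary outcome, and the discard rule mainly on earlier secondary and exploratory measures.

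**The case against.** The strongest reply is that the rest of the Protocol keeps poor compliers in. A missed assessment does not affect participation (Assessment Timeline, both arms). Missed home sessions are expected and rescheduled where possible. Non-compliance pauses payments, which later resume, and the example given there is surveys, which does not single out the intervention arm (Compensation for Participation in Research Activities). Compliance is to be summarised by arm, and the dose-response analysis uses variation in the number of visits. Systematic removal of poorly engaged intervention families is not what the document describes. This stands as a limit on how likely the problem is. It does not remove the discretion, which the withdrawal section grants without criteria.

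Second, the PICU and instability rules apply to both arms, and the Protocol states no added risk over standard physical therapy. This also stands: such withdrawals bias the contrast only if they, or the prognosis of the infants withdrawn, differ by arm. Otherwise they cost numbers and generalisability.

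Third, an analysis set may be defined in a statistical analysis plan that is not available here. That is fair as to the analysis set, and nothing in the Data analysis section excludes withdrawn infants or moves anyone between arms. But no analysis plan can recover discarded data or a 12-month score never collected.

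A reader might also infer that most withdrawn infants would have a 12-month score anyway, because the test is routine. Table 1 shows that the test is routine, not that withdrawn infants attend, and Sharing Results with Participants itself anticipates missed clinic visits.

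**Conclusion.** The point holds as a possibility that the Protocol creates, not as a certainty. After randomisation, in an open-label trial, infants can be removed from follow-up for reasons related to prognosis and, for compliance, possibly related to arm. The groups with a primary outcome may therefore differ from those randomised.

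Two stronger readings are tempting and are not supported. One is that the compared groups are necessarily no longer those randomised: discretionary withdrawal is permitted rather than required, data may be kept, and removal may be balanced. The other is that researchers could pick which primary scores to keep: the discard sentence hardly reaches the 12-month score.

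The size is unknown. It runs from no bias, with equal removal and equal gaps, to 2.25 points and a type I error of about 15% in the most extreme one-arm illustration shown. These figures rest on assumed p and D, 77 evaluable per arm and SD 15; they are not predictions. The wording is still worth correcting now, because the change is cheap and the lost outcomes cannot be restored later.

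**What to change.** Amend Withdrawal of Participants, with matching consent wording, as follows:

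- State that stopping or pausing study therapy, for whatever reason, does not end follow-up.
- Seek the 12-month Bayley-4 for every randomised infant unless the caregiver withdraws consent for follow-up, using the routine clinic visit where it takes place.
- Analyse infants in the arm to which they were assigned.
- Replace the sentence on scientific relevance with a rule that all data collected before withdrawal of consent are kept and analysed.
- Report withdrawals and their reasons by arm.

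The clinical grounds for pausing or stopping therapy are left to the investigators.

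The cost is Protocol and consent wording, plus some effort to obtain 12-month scores for infants who have stopped therapy. The sample size does not change.

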# Risks to Participants

This is a non-invasive, minimal risk study that does not involve collection of specimens. Potential risks and associated prevention or amelioration strategies are listed below.

Risk of harm due to intervention or assessment procedures

There is no significant increase in risks associated with participation in intervention sessions compared to standard physical therapy sessions. Some potential risks include:

For infants who are intubated, there is small risk of unplanned extubation. This will be minimized by the presence of the study nurse who will monitor the infants position and stability during the therapy sessions. For infants with respiratory or nutritional support (e.g., nasal cannula, NG, or G-tubes) there is a small risk of pulling the tube out of position or site irritation/bleeding during the intervention, standard of care therapy, or assessments. Care will be taken in handling of the infant at all times, and any indication of physiological changes that do not self-resolve or any additional concerns will be immediately reported to the study team and/or medical assistance will be requested, as appropriate. All study staff will be appropriately trained, and experienced at working with infants.

If a child has surgery, the intervention will be paused and surgical team clearance will be obtained, as appropriate before resuming study activities. If a child undergoes a procedure to remove a G-tube, study therapists will follow-up with the surgical team and modify the intervention or assessments based on their guidance. All surgical interventions will be documented.

Additional risks to participation include infant skin irritation, fatigue, or frustration. Intervention and assessment sessions will be completed according to infant tolerance. Changes in behavior state or stress cues will result in modification of the therapy session, as needed. Any loss of balance/falls with upright activities (e.g. stepping) will not be considered adverse events, as they are developmentally appropriate.

All assessments are standard infant outcome measures and as such have no known risks to the infant.

Risk of infant distress while wearing sensors

Risks associated with the use of the wearable sensor are minimal. Bluetooth technology is commonly used in hospitals, and it is compliant with FDA guidelines as well as FCC regulations. Though not expected, infants might experience discomfort or skin irritation from wearing the sensors. Based on infant response, the study team or caregiver(s) may request the sensor removal at any time. During the NICU phase, infants will be continuously monitored by telemetry and/or NICU staff. If an infant demonstrates significant distress, sensor use will stop and calming activities will be used to minimize infant distress. If the infant continues to express discomfort or distress, sensor data will not be collected at that study visit. The study team will monitor for signs of discomfort or skin irritation, as noted above, during study visits performed in the home or clinic.

Risk of skin irritation due to sensor placement

The Neonatal Skin Condition Scale (NSCS), an assessment used to objectively evaluate an infant’s skin integrity based on level of dryness, erythema, and breakdown, will be used as a safety measure to check for adverse effects due to sensor-skin contact on subjects in the NICU. A baseline NSCS score will be obtained by NICU/study staff before sensors are placed on the infant, as well as immediately after removal of the sensors and 30 minutes after removal of the sensors. Additional evaluation may be completed, as needed.

Risk of Caregiver discomfort when answering questions about their infant or themselves

Answering survey questions about their infant’s abilities or challenges, or the impact of these on the family and caregiver’s wellbeing may be uncomfortable. Caregivers will be advised that they do not have to answer any questions that they do not wish to answer.

